### Biochemical verification

Expired CO will be assessed at baseline, post-training, and at 6-week follow up using a Carbon Monoxide Monitor (piCO™ Smokerlyzer®; Bedfont Scientific Ltd).

### Behavioral and self-report measures

To track daily smoking and possible changes in nicotine consumption, participants are asked to self-monitor their smoking behavior via a cigarette-tracking app, which was specifically designed for the purpose of this study. That is, participants are required to download a native journaling application and are instructed to log cigarettes during or directly after smoking. The data will then be charted on the phone and on the companion website to which it is automatically synchronized. In addition, participants will be asked to estimate their average daily nicotine consumption at pretest, post-training and follow up.

The questionnaire measures will include the Fagerström Test for Nicotine Dependence (FTND) [46] (German version: [47]), the Stages of Change Scale [48] (German version: [49]), the Thoughts About Abstinence Scale [50], attitudes toward smoking based on Swanson et al. [51], the Barratt Impulsiveness Scale (BIS) [52], and the Eysenck Personality Questionnaire - Revised (EPQ-R) [53]. In addition, participants indicate their level of cigarette craving on a 6-point Likert-scale ranging from 0 (“not at all”) to 5 (“very high”). Questionnaire measures will be used to examine group differences at baseline and to assess any changes across the course of the study. At posttest, participants in the experimental condition will be also required to evaluate the app-AAT training and indicate their awareness about the training contingency.

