### Outcome measures

We focus on two primary outcome measures: (1) changes in smoking-related approach biases with regard to smoking stimuli presented during training (measured in milliseconds) and (2) reductions in self-reported daily cigarette smoking (measured in number of smoked cigarettes per day). Primary time points include post-training and follow-up assessments. Secondary outcome measures are (1) changes in smoking-related approach biases with regard to untrained pictures (close generalization), (2) changes in approach biases for positive pictures, (3) changes in other cognitive biases as measured by the visual dot-probe task and the Implicit Association Task (IAT) (broad generalization), (4) self-monitored smoking behavior using a cigarette tracking app, (5) biochemically verified abstinence rates defined as point prevalence with a 7-day window prior to the assessment point, (6) expired CO, and (7) other self-reported smoking behavior.

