### Intervention

Prior to randomization, participants will receive behavioral counseling and psychoeducation containing information on nicotine addiction and maintenance and short-term and long-term effects associated with cigarette smoking (about 90 min). Afterwards, smokers will be handed a self-help book (a German copy of *The easy way to stop smoking* by Allen Carr) to aid smoking cessation. Finally, participants will be instructed to record cigarettes smoked throughout the day for the entire study period of 6 weeks. Therefore, our behavioral interventions for smoking cessation include brief behavioral counseling, a self-help book, and the instruction to self-monitor smoking. Taken together, these three interventions constitute the TAU condition. Participants allocated to the experimental condition are then given access to the AAT-training app and are instructed to train at least once per day for 14 consecutive days. Participants perform practice training with the researchers to ensure that the training handling and concepts have been fully understood. To ensure compliance, participants will receive daily reminders via short message service (SMS) to complete the training. After completion of the study (after 6-week follow-up assessment), control condition participants will receive access to the training app.

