To test whether the app training leads to changes in the secondary outcome measures, parametric and non-parametric statistical tests will be administered where appropriate. Close training generalization will be investigated via a 2 (condition: app-training vs control) × 2 (image content: smoking vs positive pictures) × 2 (generalization: trained vs untrained pictures) × 3 (time: baseline, posttest, follow up) mixed-design ANOVA. The 2 (condition) × 3 (time) mixed-design ANOVA will be performed separately for attentional and association biases. Multilevel modeling (MLM) will be used to estimate the growth curve for nicotine consumption as measured with the cigarette training app over time (throughout the entire study period from baseline to follow up). Time will be modeled as a continuous variable. The major advantage of MLM is that it increases power and generalizability by including all individuals regardless of missing data. To examine whether the app-AAT training leads to increased abstinence rates, for each following time point, a separate chi-square test will be carried out with the binary outcome variable (smoking vs nonsmoking) as the parameter of interest. To test the effect of training on other smoking-related variables (i.e., CO, craving, FTND, smoking attitude, motivation to quit), a 2 (condition) × 3 (time) repeated measures multivariate ANOVA (MANOVA) will be conducted. MANOVA with a significant result will be followed up with both univariate tests and discriminant factor analysis. That is, ANOVA will be carried out separately on each of the dependent variables. These analyses will in turn be followed up using contrasts. In addition, discriminant analyses will be applied, which take linear combinations of the dependent variables into account, thereby complementing univariate approaches.

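### As described, the cigarette log has no entry for a smoke-free day, so the growth curve for secondary outcome 4 cannot separate abstinence from a lapse in logging

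*Protocol article*

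**What the plan says.** Under Intervention, all "participants will be instructed to record cigarettes smoked throughout the day for the entire study period of 6 weeks". Under Behavioral and self-report measures, the log is kept in an app built for this study, and participants are "instructed to log cigarettes during or directly after smoking". No entry for a smoke-free day and no end-of-day confirmation is described.

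Under Outcome measures, "self-monitored smoking behavior using a cigarette tracking app" is secondary outcome 4. Data preparation and planned analyses states that "Multilevel modeling (MLM) will be used to estimate the growth curve for nicotine consumption" from baseline to follow-up, with time continuous. It gives as the main advantage of this model "including all individuals regardless of missing data". It states no rule for a day without entries.

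Separately, participants estimate their average daily consumption at each of the three visits. Under Sample size, the secondary outcomes are called explorative.

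**The concern.** Logging is triggered by the event being counted. A day on which the participant did not smoke and a day on which the participant smoked but did not log leave the same empty record. In a cessation trial empty days should become more frequent as treatment works, so the ambiguity falls on the effect being sought.

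A multilevel model handles missing days only if they can be identified as missing. Here they cannot. If empty days are dropped, whether a day is observed depends on its own value (zero is never observed), and a missing-at-random assumption does not cover that. A participant who quit at once and stayed abstinent would contribute no rows at all. If empty days are filled with zero, a lapse in logging counts as abstinence. No later analysis rule can recover a zero that was never captured.

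**Working it through.** The plan gives no figure for this outcome; its sample-size calculation covers the primary outcomes only and is not affected. The check therefore uses assumed values, with ranges.

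**Assumptions (not in the documents).** m = 12 cigarettes on a smoking day. a = share of abstinent days, 10 to 30%. u = share of smoking days left unlogged, 10 to 30%. Differences are training minus control.

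**Formulas.**
- True mean per day: m(1 − a).
- Empty day coded missing: only logged smoking days remain, so the mean is m, whatever a is.
- Empty day coded zero: m(1 − a)(1 − u).

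**1. Empty = missing, real effect.** Abstinent days 30% in training, 10% in control.
- True: 12 × 0.7 − 12 × 0.9 = 8.4 − 10.8 = −2.4 per day.
- Estimated: 12 − 12 = 0.
- The level is overstated by 12 − 10.8 = 1.2 to 12 − 8.4 = 3.6 per day.

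This loss needs no difference in logging between arms.

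**2. Empty = zero, no real effect.**

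| a (both arms) | u training | u control | False difference per day |
|---|---|---|---|
| 10% | 10% | 10% | 0 |
| 10% | 10% | 30% | 10.8 × 0.9 − 10.8 × 0.7 = +2.16 |
| 10% | 30% | 10% | 10.8 × 0.7 − 10.8 × 0.9 = −2.16 |
| 30% | 10% | 30% | 8.4 × 0.9 − 8.4 × 0.7 = +1.68 |
| 30% | 30% | 10% | 8.4 × 0.7 − 8.4 × 0.9 = −1.68 |

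**3. Empty = zero, real effect of −2.4.**
- Equal logging (u = 10% in both arms): 7.56 − 9.72 = −2.16.
- Training logs 20 points better: 7.56 − 7.56 = 0.
- Training logs 20 points worse: 5.88 − 9.72 = −3.84.

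**4. Slopes.** Steps 1 to 3 concern levels, whereas the plan fits a curve over time. A simulation covered 42 days with 4,000 participants per arm and Poisson counts with mean 12 on smoking days. A straight line was fitted to the daily arm means; slope differences are in cigarettes per day per week.

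*Real effect.* The abstinent share rises from 0 to 40% in training and to 20% in control; the unlogged share rises from 5 to 35% in both arms.
- True slope difference: −0.40 (by arithmetic, 12 × 0.20 × 7/41 = 0.41).
- Empty = zero: −0.25.
- Empty = missing: about 0.

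*No real effect.* The abstinent share rises to 20% in both arms; empty = zero.
- Training logs better throughout (unlogged share ends at 15% against 35%): +0.31.
- Training logs worse throughout (the reverse): −0.33.
- Training logs better only in the first 14 days, then falls back to 35% unlogged by the end: −0.07.

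**The case against.** The strongest objection is that the article gives the instruction to participants, not the app's full functions. A smoke-free-day entry or a rule for empty days may stand in the full protocol or the SAP. That is fair: a reader might infer that the app cannot record a zero, and the article does not say so. The point therefore holds for the log as described. It is still more than an omitted detail. An analysis rule for empty days can be written later, but a zero must be captured on the day, and the article makes a positive claim about missing data that depends on it.

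Several stronger readings are not supported:
- **The SMS reminders make logging differ by arm.** In the article "participants will receive daily reminders via short message service (SMS) to complete the training"; they are not reminders to log. Only the training arm can receive them, because "control condition participants will receive access to the training app" only after the follow-up. But that arm is "instructed to train at least once per day for 14 consecutive days", about a third of the 42 logged days, and controls also use a study app for all six weeks. Spill-over to logging is conjecture, and the matching simulation gave only −0.07 per week.
- **A fixed gap in completeness biases the curve by that amount.** A 10-point gap at 12 cigarettes gives 12 × 0.10 = 1.2 per day under zero-filling, but this shifts the level. With stable smoking it adds nothing to the slope.
- **Adjusting for baseline would remove 25% of the variance.** That squares the r = 0.5 under Sample size, which is assumed for repeated measures of the primary outcomes, not for baseline self-report against logged counts.
- **The main smoking result is affected.** The primary cigarette outcome appears to rest on the estimates made at the visits, and abstinence has its own biochemically verified outcome.

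**Conclusion.** The point stands for the cigarette log as described. Smoke-free and unlogged days are indistinguishable, and the stated advantage of the multilevel model does not extend to them. In the assumed ranges, coding empty days as missing turns a true −2.4 cigarettes per day into 0. Coding them as zero produces a false difference of 1.68 to 2.16 per day when completeness differs by 20 points between arms, with the sign set by which arm logs better. Even with equal but declining logging, zero-filling shrinks a true slope difference of −0.40 per week to −0.25.

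These sizes rest entirely on assumed smoking and logging rates. The documents do not show that logging will differ between arms. The hiding of an abstinence effect when empty days are dropped needs no such difference. The reach is secondary outcome 4, which the plan treats as exploratory. It is nevertheless the only daily prospective measure of smoking, and the fault cannot be repaired after collection.

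**What to change.** Unless the app already does this (in which case the article should say so):
- Add a once-daily confirmation of the day's total, including zero, in both arms. Any prompt to log should be identical in both arms.
- Code a confirmed zero as zero and an unconfirmed day as missing, and state this rule with the growth-curve analysis.
- Report logging completeness by arm over the six weeks. Unconfirmed days may still not be missing at random, but the reader can then see how many there are and where.
- Optionally, add self-reported baseline cigarettes per day to the multilevel model as a precision covariate, without promising a size of gain.

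Cost: a small change to a purpose-built app. According to Trial status, the trial had not started at submission, so this was possible before recruitment. Participants spend a few seconds a day. Self-monitoring is one of the three components of treatment as usual, so daily confirmation strengthens it slightly; applying it equally keeps the comparison between arms fair.

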### Procedure

A time schedule of enrollment, assessment visits, and AAT-app trainings for participants is shown in Fig. 2. During the first laboratory session (baseline; around 180 min) participants give informed consent and take part in a brief behavioral intervention for smoking cessation (TAU). Participants then complete the cognitive bias assessments, the questionnaire measures, and the carbon monoxide breath test. Smokers in the training condition (TAU + training) are given access to the AAT-training app. Participants are instructed to perform the app training on a daily basis for 14 consecutive days. During the second (post-training) and final (6-week follow up) laboratory session, participants complete cognitive bias assessment tasks, questionnaire measures, and the CO breath test. Participants in the experimental condition are asked to evaluate the training and indicate their awareness about training contingencies. Individuals randomized to the control condition will receive access to the training app upon completion of the final follow-up measure. Training data from these participants will not be analyzed.

**Fig. 2 Fig2:**
[figure not shown]
Schedule of enrollment, assessments and interventions (SPIRIT)

### Data preparation and planned analyses

Multiple imputation of missing data will be performed for intention-to-treat (ITT) analyses [54]. To analyze changes in cognitive biases, error trials will be excluded from further analyses. Median RTs will be used to minimize the influence of outliers.

To investigate whether the app training leads to changes in the primary outcome measures, two separate 2 (condition: training vs control) × 3 (time: baseline, post-training, follow up) mixed design analysis of variance (ANOVA) will be performed. Changes in smoking approach biases and self-reported daily nicotine consumption will constitute the primary dependent variables. A separate univariate test will determine if there are significant differences in smoking-related approach biases or average nicotine consumption at baseline between the app training and the control group. Due to the random assignment to the experimental or to the control group, we expect a priori group differences to be small. Nevertheless, chance baseline imbalance between treatment arms will be taken into account, when evaluating training effects. Substantive hypotheses will be tested by means of follow-up simple effects analyses. Here, we compare means in the app training and control group (posttest and follow up, respectively), while controlling for baseline approach bias and nicotine consumption levels. We apply a mixed design ANOVA as one factor (a fixed effects factor) is a between-subjects variable (here, condition) and the other (a random effects factor) is a within-subjects variable (here, time).

To test whether the app training leads to changes in the secondary outcome measures, parametric and non-parametric statistical tests will be administered where appropriate. Close training generalization will be investigated via a 2 (condition: app-training vs control) × 2 (image content: smoking vs positive pictures) × 2 (generalization: trained vs untrained pictures) × 3 (time: baseline, posttest, follow up) mixed-design ANOVA. The 2 (condition) × 3 (time) mixed-design ANOVA will be performed separately for attentional and association biases. Multilevel modeling (MLM) will be used to estimate the growth curve for nicotine consumption as measured with the cigarette training app over time (throughout the entire study period from baseline to follow up). Time will be modeled as a continuous variable. The major advantage of MLM is that it increases power and generalizability by including all individuals regardless of missing data. To examine whether the app-AAT training leads to increased abstinence rates, for each following time point, a separate chi-square test will be carried out with the binary outcome variable (smoking vs nonsmoking) as the parameter of interest. To test the effect of training on other smoking-related variables (i.e., CO, craving, FTND, smoking attitude, motivation to quit), a 2 (condition) × 3 (time) repeated measures multivariate ANOVA (MANOVA) will be conducted. MANOVA with a significant result will be followed up with both univariate tests and discriminant factor analysis. That is, ANOVA will be carried out separately on each of the dependent variables. These analyses will in turn be followed up using contrasts. In addition, discriminant analyses will be applied, which take linear combinations of the dependent variables into account, thereby complementing univariate approaches.

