### Sample size

A priori power analyses were conducted using G*Power 3.1 (open-source software [34]). Previous research investigating the effectiveness of CBM training identified a small-to-moderate effect size [21, 35]. We conducted a power analysis for a 2 × 3 mixed design ANOVA to detect a small-to-moderate effect (Cohen’s *d* = 0.30, α = 0.05) for the interaction between experimental condition and time for each primary outcome and time point. Power of 0.80 and *r* = 0.5 for correlation between the repeated measures was assumed. Results indicated that 74 participants in total would be needed. Due to an expected attrition rate of approximately 25% at follow up (defined as dropout at any time point after completing the baseline assessment), we decided to include 100 participants, that is 50 per condition.

We would like to stress that we performed power calculations for primary outcomes exclusively. With regard to secondary outcome measures, we emphasize that the study is explorative, meaning that any significant findings on these outcome variables should be interpreted with caution until tested in further confirmatory RCTs.

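### The powered primary test is a condition × time interaction that counts baseline as an outcome; it is valid, but a joint baseline-adjusted test of the two later visits has more power from the same data

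*Protocol article*

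**What the plan says.** Under Outcome measures, the protocol article names post-training and follow-up as the primary time points; baseline is not among them.

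Under Data preparation and planned analyses, the test of whether the app changes the primary outcomes is that "two separate 2 (condition: training vs control) × 3 (time: baseline, post-training, follow up) mixed design analysis of variance (ANOVA) will be performed". The section then adds a baseline comparison: "A separate univariate test will determine if there are significant differences in smoking-related approach biases or average nicotine consumption at baseline". It expects such differences to be small because of randomisation and says that chance imbalance will be considered when training effects are judged. Lastly, it assigns the substantive hypotheses to follow-up simple effects, which compare the arms at post-test and at follow-up with baseline controlled.

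Under Sample size, power is computed "for the interaction between experimental condition and time for each primary outcome and time point", with the inputs "Power of 0.80 and *r* = 0.5 for correlation between the repeated measures was assumed" and Cohen's d = 0.30 at α = 0.05. The outcome is "Results indicated that 74 participants in total would be needed". The section gives no power for the baseline-adjusted comparisons.

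**The concern.** The interaction compares profiles over three time points, one of which precedes any access to the app. It uses the baseline measurement as a response and leaves the arms free to differ there, although randomisation makes that difference zero in expectation. In effect it compares changes from baseline. When baseline and later values are only moderately correlated, subtracting baseline adds noise that regression on baseline would remove.

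The baseline significance test adds nothing. Under sound randomisation any baseline difference is due to chance, as the section itself accepts, and a p-value does not show whether adjustment would help.

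What is at stake is efficiency. The trial is small, expects small-to-moderate effects and plans for an "expected attrition rate of approximately 25% at follow up". It already collects the baseline values that would sharpen the primary comparison, but the test that carries the power statement does not use them as a covariate.

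**Working it through.** **Inputs.** From Sample size: d = 0.30, α = 0.05, target power 0.80, r = 0.5, N = 74 before attrition. From the analysis section: two arms, three time points. Assumed here: compound symmetry with unit variance, 37 per arm, complete data, and the pattern of the effect over time, which the article does not give.

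**1. Reproducing 74.** With f = d/2 = 0.15 (inferred; the article does not state f) and m = 3 measurements, the noncentrality is

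λ = f²·N·m/(1 − r) = 0.0225 × 74 × 3/0.5 = 9.99,

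on 2 and 2(N − 2) = 144 df. Power is 0.806. N = 72 gives 0.795, so 74 is the smallest equal-arm total that reaches 0.80. Entering f = 0.30 would give 20, so f = 0.15 is the value that matches.

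**2. The effect that f = 0.15 implies.** For a difference δ (in SD) equal at both later visits and zero at baseline, the interaction has λ = N·δ²/[6(1− r)], which at r = 0.5 is N·δ²/3. Setting 74·δ²/3 = 9.99 gives δ² = 0.405 and δ = 0.64.

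**3. Baseline-adjusted joint test.** Given baseline, each later visit has variance 1 − r² = 0.75, and the two visits have covariance r − r² = 0.25. For difference vector δ and this residual covariance matrix S, λ = (N/4)·δ′S⁻¹δ. At r = 0.5:
- equal effect at both visits: λ = N·δ²/2, which is 1.5 times the ANOVA value;
- effect at one visit only: λ = 0.375·N·δ², against N·δ²/3 for the ANOVA, which is 1.125 times.

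**4. Power at N = 74, r = 0.5** (adjusted test on 2 and N − 4 = 70 df):

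| True difference | Pattern | λ, ANOVA | λ, adjusted | Power, ANOVA | Power, adjusted |
|---|---|---|---|---|---|
| 0.64 SD (f = 0.15) | both visits | 9.99 | 14.99 | 0.806 | 0.934 |
| 0.64 SD | one visit | 9.99 | 11.24 | 0.806 | 0.844 |
| 0.50 SD (assumed) | both visits | 6.17 | 9.25 | 0.587 | 0.764 |
| 0.50 SD | one visit | 6.17 | 6.94 | 0.587 | 0.631 |
| 0.30 SD | both visits | 2.22 | 3.33 | 0.242 | 0.340 |

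With 142 instead of 70 denominator df, the 0.764 becomes 0.773, hence 76–77%. Simulation of the ANOVA with 20,000 runs gave 0.805 at 0.64 SD and 0.593 at 0.50 SD.

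**5. Dependence on r.** The effect is rescaled at each r so that the ANOVA stays at 0.806:

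| r | Adjusted, both visits | Adjusted, one visit |
|---|---|---|
| 0.3 | 0.974 | 0.873 |
| 0.5 | 0.934 | 0.844 |
| 0.7 | 0.882 | 0.822 |
| 0.8 | 0.854 | 0.813 |

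**6. In participants.** At r = 0.5 and 0.64 SD at both visits, 80% power needs 52 participants in total with the joint adjusted test, against 74 with the interaction.

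**The case against.** The strongest reply is that the better comparison is already in the plan. The simple effects compare the arms at each later visit with baseline controlled, and the substantive hypotheses are assigned to them. If those two comparisons are read as decisive and tested with a Bonferroni correction over the two visits (an assumption; the article states none), simulation at 0.50 SD, r = 0.5 and N = 74 finds at least one significant in about 77% of runs. That equals the joint test, so on this reading almost no power is lost. This stands as a limit on the point. It does not remove it, because the test that is powered and set to show whether the training works is still the interaction.

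Three stronger readings are tempting, and the document does not support them:
- *The simple effects run only after a significant interaction.* The word follow-up may suggest an order, but no condition is written. For the MANOVA, the same section does write one.
- *Baseline handling depends on the data and makes the primary analysis arbitrary.* Baseline control in the simple effects is unconditional. Nothing ties it to the result of the baseline test, which is redundant and no worse than that.
- *The ANOVA mishandles dropout.* Multiple imputation is planned for the intention-to-treat analyses. The remark that "The major advantage of MLM is that it increases power and generalizability by including all individuals regardless of missing data" concerns the series from the cigarette-tracking app, which is a different data structure.

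It can also be said that covariance structure and estimation method belong in an analysis plan. That is fair. The choice and order of the tests, however, are fixed in the article.

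**Conclusion.** The point holds as one of efficiency. The planned ANOVA is not invalid, and 74 is right for it. The joint baseline-adjusted test had more power in every case computed. At N = 74 and r = 0.5 the gain is about 13 points at the effect size behind the 74 (93% against 81%) and about 18 points at an assumed 0.50 SD, both for an equal effect at the two visits. For an effect at one visit it is about 4 points, and at r = 0.8 it falls to about 5 points (both visits) or 1 point (one visit).

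These figures rest on compound symmetry, complete data on 74 participants and assumed effect patterns. A reader might infer that the plan leaves out baseline adjustment or that its primary result would be unreliable. Neither follows: the adjustment is planned, but not in the test that carries the power statement.

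**What to change.** For each primary outcome, make the planned baseline-adjusted comparisons the primary test, within one longitudinal model. Post-training and follow-up are the responses. The fixed effects are condition, visit, condition × visit, baseline value and baseline × visit, with unstructured within-participant covariance. Test the two adjusted differences jointly on 2 df and report each with its 95% confidence interval. A single average over both visits should not replace the joint test: with an effect of 0.64 SD at one visit only, its power drops to 0.48.

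State that baseline is always adjusted for, and delete the baseline significance test. Restate the power calculation for the new primary test.

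The cost is a reworded analysis section and slightly more modelling work. No data collection changes. The article says the trial had not started at submission, so at that stage the change could be prespecified.

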##### Approach bias assessment

Automatic approach biases for smoking-related stimuli will be measured by means of the standard version of the nicotine-AAT (see [18]). At baseline, 25 smoking-related and 25 positive images derived from Baird et al. [25] appear on a computer screen. To test whether training effects can be generalized to pictures other than those used during bias retraining, 12 out of the 25 pictures contain images not shown during app-AAT training (close generalization). Similar to the training, images are tilted 3° to the left or 3° to the right. A joystick (Logitech Extreme 3D) is connected to the computer and participants are told to use the joystick to push images rotated to the right and to pull images rotated to the left. As a result, images shrink or grow in size dependent on arm movement. For the purpose of bias assessment, smoking and control pictures have to be pulled and pushed equally often. Each picture is shown once in push-away format und once in pull-closer format, resulting in 100 assessment trials.

An approach bias in inferred from faster picture pulling than picture pushing. That is, an approach bias score is calculated by subtracting median RTs for pulling a picture from median RTs for pushing the exact same picture. The RT is defined as the time a participant needed to execute the correct full joystick movement. Accordingly, a positive value indicates an approach tendency toward a picture category, whereas a negative value indicates an avoidance tendency. Approach biases are computed for each of the image categories (smoking vs positive; trained vs untrained) and for each of the laboratory sessions (baseline, post-training, and follow up), resulting in four bias scores at three different time points.

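### The four-way ANOVA planned for close generalization has no omnibus term that tests the stated outcome, the change in approach bias for untrained smoking pictures

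*Protocol article*

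**What the plan says.** Under Outcome measures, secondary outcome (1) is "changes in smoking-related approach biases with regard to untrained pictures (close generalization". The primary bias outcome in the same section concerns smoking stimuli that were shown during training, so the untrained smoking score is a separate endpoint.

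Under Approach bias assessment, the laboratory task can separate the two: "12 out of the 25 pictures contain images not shown during app-AAT training (close generalization". Scores are computed by content (smoking, positive) and by trained/untrained status, "resulting in four bias scores at three different time points".

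Under Data preparation and planned analyses, the analysis is: "Close training generalization will be investigated via a 2 (condition: app-training vs control) × 2 (image content: smoking vs positive pictures", continued as "2 (generalization: trained vs untrained pictures) × 3 (time: baseline, posttest, follow up) mixed-design ANOVA". No main effect, interaction or contrast is identified as the test. The next sentence plans a plain 2 (condition) × 3 (time) ANOVA for each of the attentional and association biases, but none for the untrained smoking score.

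The Sample size section powers the primary outcomes only and describes the study as explorative for secondary outcomes.

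**The concern.** The outcome asks whether training, compared with control, changes the bias on untrained smoking pictures. The trained/untrained factor in the ANOVA asks something else: whether the training effect is the same size on the two picture sets. When transfer is perfect the answer is no difference, so the interaction is null exactly when generalization is best. It is also null when training has no effect. The remaining terms mix untrained with trained pictures and can be significant because of the trained ones.

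The Background treats limited generalization as one of the main explanations for mixed findings in this field, so a conclusion about it will be read with interest. As planned, that conclusion would have to rest on a term that does not answer the question, or on a contrast chosen after the data are seen.

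**Working it through.** **1. What each term estimates.** Let S_T, S_U, P_T and P_U be the training-minus-control change from baseline for smoking-trained, smoking-untrained, positive-trained and positive-untrained pictures. The stated outcome is S_U. Up to scale, the terms involving condition and time are:

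- condition × time: S_T + S_U + P_T + P_U
- condition × content × time: (S_T + S_U) − (P_T + P_U)
- condition × trained/untrained × time: (S_T − S_U) + (P_T − P_U)
- four-way: (S_T − S_U) − (P_T − P_U)

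None equals S_U. With full transfer (S_U = S_T, P_U = P_T) the last two are zero. With no training effect all four are zero. With no transfer (S_U = P_U = 0) the first two still contain S_T and P_T. This step needs no assumption about variances.

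**2. The protocol's own figure.** The Sample size section gives d = 0.30 (f = d/2 = 0.15), α = 0.05, power 0.80, correlation 0.5 and a total of 74. For the within-between interaction with k = 2 groups and m = 3 times, λ = f²·N·m/(1 − r) = 0.0225 × 74 × 3/0.5 = 9.99, with df 2 and 144. Power is 0.806, so 74 reproduces.

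**3. Effect used in the simulation.** If the shift d* is the same at post-training and follow-up, the pattern (0, d*, d*) gives f² = (6/27)d*²/4 = d*²/18. Hence d* = 0.15 × √18 = 0.64 SD. This value is not stated in the protocol; it follows from f = 0.15 and the assumed pattern.

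**4. Simulation.** N = 74, 3,000 runs per scenario, unit-SD scores, time correlation 0.5. Assumed, because not in the document: correlation between trained and untrained scores of 0.2, 0.5 or 0.8; correlation between contents of 0.2; positive pictures either unaffected or shifted equally in the opposite direction. The table gives rejection rates in %, with the three values in each cell for correlation 0.2 / 0.5 / 0.8.

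| Test | No transfer | Half | Full |
|---|---|---|---|
| Four-way, only smoking shifts | 40.7 / 57.9 / 95.0 | 12.7 / 18.5 / 41.7 | 4.6 / 4.5 / 5.0 |
| Four-way, both contents shift | 94.4 / 99.5 / 100 | 40.1 / 59.4 / 94.3 | 5.2 / 4.5 / 5.5 |
| Condition × trained/untrained × time, smoking pictures only* | 59.2 / 79.7 / 99.7 | 18.6 / 27.1 / 59.0 | 4.6 / 4.5 / 5.3 |
| Condition × content × time, only smoking shifts | 29.3 / 23.4 / 19.1 | 56.4 / 45.9 / 39.6 | 82.4 / 73.8 / 63.1 |
| Condition × content × time, both shift | 82.0 / 72.4 / 63.5 | 99.5 / 97.8 / 95.6 | 100 / 100 / 99.8 |
| Direct 2 × 3 on untrained smoking* | 5.0 / 5.4 / 5.3 | 27.0 / 25.5 / 27.7 | 80.6 / 81.9 / 80.8 |

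*Runs in which only smoking pictures shift; the other runs are similar.

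Terms with trained/untrained fall to about α as transfer becomes complete. Condition × content × time rejects in 19–82% of runs with no transfer at all. Only the direct test starts at α and rises with the stated outcome.

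**The case against.** **No stated rule makes a null a success.** A reader might infer that a non-significant interaction will be reported as generalization. The article does not say so; it only says the question will be investigated with this ANOVA. That objection stands, and the risk is one left open by the unnamed term.

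**The contrast could be left to an analysis plan.** This is a condensed article, and follow-up contrasts are often specified elsewhere. The point, however, is a mismatch between an outcome and the analysis named for it, and the same paragraph does name the simpler, fitting analysis for the other two biases.

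**Simple effects already cover it.** The section also says "Substantive hypotheses will be tested by means of follow-up simple effects analyses", comparing groups at posttest and follow-up with baseline adjustment. Applied to the untrained smoking score, that would be essentially the remedy. But the sentence belongs to the primary-outcome paragraph and is not extended to the generalization analysis.

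**Cancellation.** Smoking and positive pictures are trained in opposite directions, so a reader might conclude that pooling them cancels the effect. Content is a factor in the model, so this affects only terms that omit it. Opposite shifts strengthen the four-way term, which then detects zero transfer in 94% or more of runs. Since change in bias for positive pictures is itself a secondary outcome, including content is reasonable.

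**Size.** It is tempting to quote a miss rate of 52–73%. That comes from one scenario: the four-way contrast with 37 per arm, a 0.64 SD effect, half of it lost on untrained pictures of both contents, and correlation q of 0 to 0.5 among the four scores (variance 4(1 − q), power 27–48%). At q = 0.8 the same contrast has 86% power. With zero transfer the contrast doubles to 1.28 and power is 78–97% for q from 0 to 0.5. The 52–73% is therefore not a general measure of the problem.

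**Conclusion.** The concern holds as a mismatch between outcome and analysis. The core is algebraic: no omnibus term of the planned ANOVA estimates the training effect on untrained smoking pictures, and a null trained/untrained interaction cannot separate full transfer from no training effect or from low power. How often partial or absent transfer would go undetected depends on unstated correlations and on how positive pictures respond, so no single error rate should be attached to it.

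The documents do not support saying that the investigators will treat a null interaction as success, or that the four-way ANOVA is useless: it can detect incomplete transfer well under some assumptions. The outcome is declared exploratory and the primary analyses are untouched, so what is at stake is the secondary conclusion on close generalization.

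**What to change.** State that close generalization is tested on the untrained smoking score, either as the training-minus-control difference at post-training and at follow-up, adjusted for baseline bias on the same pictures, or as the 2 × 3 condition × time test already planned for the attentional and association biases. Report the group differences with 95% CIs. Because the direct test has only about 26–28% power under half transfer, a non-significant result should not be read as absence of transfer either.

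Keep the four-way ANOVA, or the trained-minus-untrained difference in effect with its CI, as a supporting description of transfer, and state that a null interaction will not be interpreted as generalization. If complete transfer is to be claimed, set an equivalence margin for that difference in advance. Report positive pictures separately as their own secondary outcome.

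The cost is a few sentences and one small extra analysis. The four bias scores are already to be computed, and no design, data collection or sample size change is needed.
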